### Outcomes Associated with Bariatric Surgery

Although no large scale, contemporary randomized controlled trials (RCTs) have examined the impact of surgery on cardiovascular morbidity or overall mortality, compelling data are available from high quality observational studies such as the Swedish Obesity Study (SOS), a matched cohort study of 2010 surgical and 2037 controls [16,17]. Compared to the poor long-term results of non-surgical therapy, surgery is the only therapy associated with substantial improvements in weight (averaging 33% after 2-3 years[18] and 16% after 10 years[16]); 15-year mortality rates (5.0% versus 6.3% in well-matched controls; HR 0.71; 95% CI 0.54 to 0.92);[19] 11-year incidence rates of first time cancers (HR 0.67; 95% CI 0.53-0.85);[17] and 7-year mortality rates from coronary artery disease (HR 0.41; 95% CI 0.21-0.78) and cancer (HR 0.40; 95% CI 25-0.65) [20]. In terms of other medical comorbidity, surgery increased remission rates for type 2 diabetes (73% versus 13%; p < 0.001; OR 5.5; 95% CI 2.2-14) in a 60-patient RCT;[21] and meta-analyses of primarily observational data has demonstrated that surgery is associated with resolution or improvement of type 2 diabetes, hypertension, dyslipidemia and sleep apnea in 70-86% of cases [18]. Additional studies demonstrate that surgery significantly (p < 0.05) improves psychosocial functioning,[22] quality of life,[23] and physical function [24].

In terms of Canadian data, a retrospective analysis of 1035 bariatric surgery patients from a single practice in Quebec reported 5-year excess weight losses of 61-75% following gastric bypass and banding [25]. In an earlier study, patients from this bariatric program (n = 1035) were also retrospectively compared with 5746 age and sex-matched controls identified using administrative data claims in Quebec (clinical variables such as height and weight were not available for controls) [26]. Mortality rates over 5 years were markedly lower in the bariatric surgery cohort compared to controls (0.68% versus 6.17%; RR 0.11, 95% CI 0.04-0.27) although the design of this study cannot rule out the very real likelihood that surgical selection bias (i.e., healthier and higher socioeconomic status patients with lower likelihood of surgical complications more likely to receive surgery) explains some if not most of these findings.

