## Methods/design

### Overall Study Design

In this prospective cohort study, consecutive and consenting patients enrolled in the Weight Wise Regional Obesity Program and without a contraindication to surgery will be enrolled. The minimum enrolment sample size will include 150 surgical patients, 200 patients receiving intensive medical therapy and 150 patients wait-listed to enter the clinic (Figure 1). The number of patients enrolled in the medical arm is larger because we anticipate an increased rate of censoring in this study arm, as some of these patients will ultimately undergo bariatric surgery within the two-year follow-up period.

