### Inclusion Criteria

1. Male or female patients in the Weight Wise Regional Obesity Program

2. 18-60 years old

3. BMI levels ≥ 35 kg/m^2 ^and a major medical comorbidity or BMI levels ≥ 40 kg/m^2^

4. Able to provide informed consent

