### Statistical Analysis and Sample Size Considerations

#### Clinical, Humanistic and Economic Outcomes in Wait-listed Patients

This analysis specifically focuses on the wait-listed group and will examine two-year change scores in each relevant outcome using the appropriate statistical methodology. Analyses will be conducted in all wait-listed patients as well as those indicating a specific interest in surgery. Examples of clinical outcomes include anthropometric indices, blood pressure, lipid profile, glycemic control, diabetes prevalence. Examples of humanistic outcomes include QOL and patient satisfaction. Economic outcomes include total and categorical costs. For example, two-year change scores will be analysed for QOL domains (e.g. SF-12, IWQoL-Lite) using appropriately calibrated and constructed linear regression models and/or analysis of variance. Because these are self-reported data collected on a semi-annual basis, we will use a "last-value carried forward" approach to handle missing data as our primary analytic strategy.

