#### Comparing Clinical and Humanistic Outcomes in Patients Treated with Surgery to Medically Treated and Wait-listed Patients

Outcomes are similar to those listed above. Two-year mean changes in continuous variables will be compared between the surgical arm and medical or wait-listed controls using unpaired t-tests for continuous outcomes and chi-squared tests for dichotomous ones. Multivariable predictors of the 2-year change in a given outcome will be identified using appropriately constructed and calibrated covariate-adjusted linear regression models for continuous outcomes or logistic regression models for dichotomous ones. Patients who cross over to another study arm (e.g., medically treated patients who undergo surgery) will be censored at the point of cross over and a last-observation-carried-forward approach to missing data will be used for the primary analysis.

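### Diabetes prevalence as an outcome nets remission against new onset and depends on each arm's baseline diabetes share; the two should be separate outcomes defined by baseline status.

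*Protocol article*

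**What the plan says.** The section on clinical, humanistic and economic outcomes in wait-listed patients says that two-year change will be examined and gives examples: "Examples of clinical outcomes include anthropometric indices, blood pressure, lipid profile, glycemic control, diabetes prevalence". It names neither remission nor new onset of diabetes.

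The section comparing surgery with medically treated and wait-listed patients opens with "Outcomes are similar to those listed above". It compares two-year mean changes in continuous variables between arms, "using unpaired t-tests for continuous outcomes and chi-squared tests for dichotomous ones". It then adds regression: "Multivariable predictors of the 2-year change in a given outcome will be identified using appropriately constructed and calibrated covariate-adjusted linear regression models", with logistic models for dichotomous outcomes. No covariates are named.

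The arms are not randomised: "150 surgical patients, 200 patients receiving intensive medical therapy and 150 patients wait-listed to enter the clinic" (Overall Study Design). Eligibility admits patients with and without diabetes: "BMI levels ≥ 35 kg/m^2 ^and a major medical comorbidity or BMI levels ≥ 40 kg/m^2" (Inclusion Criteria). Eligibility For Surgery gives type 2 diabetes as one example of such a comorbidity.

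**The concern.** Prevalence is a stock. At two years it contains patients who were diabetic at the start and stayed so, plus new cases, minus those who remitted. The two flows come from different people and answer different questions. For surgery, the interest is mainly in remission, and the background evidence that the article cites is itself a remission rate: "surgery increased remission rates for type 2 diabetes (73% versus 13"%. For the wait list, the deterioration that Objective 1 looks for is new onset. One net figure shows neither.

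The arms can also start with different diabetes shares, because they are formed by clinical selection and by place in the queue. A result on prevalence then partly reflects who entered each arm.

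**Working it through.** **The plan's own figure.** None is stated for diabetes or glycaemia. The only sample size in the between-arm section is for body weight (13 patients). It reproduces as 10 per arm x 1.3 and does not bear on this point.

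**Inputs.**
- From the article: 150 surgical and 150 wait-listed patients; 30% attrition (Sample Size Considerations), so 150 x 0.7 = 105 completers; remission 73% v 13% (background section).
- Assumed, because the article gives none: baseline diabetes share b between 20% and 60%; two-year onset o of 1% after surgery and 3% to 5% otherwise; wait-list remission r of 10% to 13%.

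**Formulas.**
- Two-year prevalence = b(1 - r) + (1 - b)o.
- Net change = (1 - b)o - b·r.
- Rejection probability of a two-sided 5% test with n per arm = Φ{[|p1 - p2| - 1.96·√(2p̄(1 - p̄)/n)] / √[(p1(1 - p1) + p2(1 - p2))/n]}.

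**Reading 1: status at two years is compared.** Suppose nobody changes.
- 45% v 30%, n = 150: [0.15 - 1.96 x 0.0559]/0.0552 = 0.73, so rejection is about 77%. With exactly these proportions observed, z = 0.15/0.0559 = 2.68 and p = 0.007. At 105 v 105, rejection is about 61%.
- 40% v 30%, n = 150: [0.10 - 1.96 x 0.0551]/0.0548 = -0.15, so rejection is about 44%. At 105 v 105, about 33%.

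The nominal rate is 5%.

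**Reading 2: change in prevalence is compared.** If nobody changes, both arms show zero and the false positive above is absent. The size of a real effect still depends on the starting share. With remission 73% and onset 1%:
- b = 30%: 0.70 x 0.01 - 0.30 x 0.73 = -0.212, about -21 points.
- b = 50%: 0.50 x 0.01 - 0.50 x 0.73 = -0.360, or -36 points.

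Identical remission and onset rates also give unequal net changes when shares differ. With remission 13% and onset 3% in both arms:
- b = 30%: 0.021 - 0.039 = -1.8 points.
- b = 50%: 0.015 - 0.065 = -5.0 points.

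This 3.2-point gap is far smaller than the 20-point gap in starting shares, but it is not zero.

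**Wait list (Objective 1), 105 completers.**
- b = 30%, onset 5%, remission 10%: new cases 105 x 0.70 x 0.05 = 3.7; remissions 105 x 0.30 x 0.10 = 3.2; net about +0.5 points.
- Range: b = 20%, onset 5%, remission 10% gives 0.040 - 0.020 = +2.0 points. b = 60%, onset 3%, remission 13% gives 0.012 - 0.078 = -6.6 points, an apparent improvement although new cases occur.

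**Cost of splitting.** At a 30% share, about 0.30 x 105 = 31 baseline diabetics per arm remain. Remission of 73% v 13% at 31 v 31 has power above 99%.

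**The case against.** The strongest reply is that the plan speaks of change. The wait-listed section frames every relevant outcome as two-year change, and the regression sentence in the between-arm section does the same. On that reading nobody tests two-year status, and the 77% and 44% figures do not apply. This stands in part. The phrase about mean changes attaches only to continuous variables, and no baseline-referenced form is given for a dichotomous outcome, so both readings are open. A reader might infer that the plan commits to a status comparison with a false-positive rate of that size; the documents do not fix that. Nor do they support saying that a real effect would be hidden: if a third of an assumed 45% remit, both arms end at 30% on status (0.45 x 2/3), but on change the surgical arm shows -15 points against 0.

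A reader might also infer that mean HbA1c change is wrongly pooled over diabetic and non-diabetic patients. Pooling is inferred only from the absence of a restriction, and a pooled mean is a valid average for the enrolled mix.

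The chi-squared test is not at fault; it suits remission and onset equally well. Covariate adjustment is planned, and including baseline diabetes could reduce the imbalance problem. It would not by itself separate remission from onset. Finally, detailed definitions may sit in an analysis plan that is not shown, so one cannot say that remission will never be reported. But the outcome named here is prevalence, and a plan that follows it inherits the netting.

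**Conclusion.** The point holds in limited form. Under either reading, diabetes prevalence combines two opposite flows and varies with the baseline diabetes share, in arms that were not randomised. A false difference from baseline imbalance alone (about 77% or 44% rejection in the illustrations) arises only if two-year status is compared. If change is compared, what remains is that one and the same remission effect appears as about -21 or -36 points according to the starting share, and that wait-list onset and remission can offset each other. All baseline shares, onset rates and wait-list remission rates are assumptions, so the sizes are illustrative; the netting follows from the definition of the outcome. The weight is minor to moderate: diabetes is one example among several clinical outcomes, no sample size depends on it, and the Objective 2 hypothesis names weight, unplanned care and quality of life.

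**What to change.** In both analysis sections, replace diabetes prevalence with two outcomes defined by baseline status: remission among patients diabetic at baseline, and new onset among those who were not. Compare arms within each set; the chi-squared test and the logistic models can stay. In the wait-listed arm, report both rates with confidence intervals. As a supplementary analysis, report HbA1c and fasting glucose change within baseline diabetics, keeping the pooled mean change.

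This is a change of wording and needs no new data. Comorbidities, medications, fasting glucose and HbA1c are collected at baseline, medications by interview during follow-up, and glycaemic parameters again at two years. The price is a smaller denominator in each set. That matters little for a remission effect of the size that the article cites. It leaves new onset imprecise, with only a few cases expected per arm, which is why confidence intervals are needed there.

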### Follow-up

Follow-up visits will be scheduled every 6 months for two years and will be performed in-person or by telephone if necessary. The final two year follow-up visit will be performed in-person.

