^1^Health Care Payor perspective includes cost categories 1-6; Public Payor perspective includes cost categories 1-7 and Societal Payor perspective includes all costs.

After informed consent is obtained, baseline data collection for consenting patients will include the following: age, sex, race, marital status, employment status, household income quintile (≤ 20 K, 20-40 K, 40-60 K, 60-80 K, ≥80 K), general medical history and obesity-related comorbidities, smoking status (current, past, never), detailed current and past medications, weight, BMI, waist circumference, blood pressure, fasting lipids, fasting glucose, HbA1c, and liver enzymes.

Body weight will be measured using a validated, calibrated scale to the nearest 0.1 kilogram after the patient has emptied his/her bladder. Subjects will wear light indoor clothing with empty pockets and no shoes. Height will be measured using a wall-mounted stadiometre. A single reading taken using an automated blood pressure monitor and using an appropriately sized blood pressure cuff will be recorded with the subject seated in a chair and after five minutes of rest.

Repeat assessment of blood pressure, body weight, and cardiovascular risk factors (cholesterol profile, glycemic parameters) will be performed at 2 years.

Additional outcomes to be collected every 6 months will include:

1. **Household income and employment status**

2. **Quality of life and utility measurement**: Health related quality of life will be measured using validated, widely-used instruments. Generic and preference-based quality of life will be assessed using the Short Form-12 (SF-12[50]) and the EuroQol-5D (EQ-5D[51]) respectively. Obesity-specific quality of life will be assessed using the Impact of Weight on Quality of Life-Lite (IWQOL-Lite) [52].

3. **Patient satisfaction: **Satisfaction with medical care will be assessed using two questions, which will be rated on a 5-point Likert Scale:

a. The medical care I have been receiving is just about perfect

b. I am dissatisfied with some things about the medical care I received.

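### For weight, blood pressure, lipids and glycaemia, which the article repeats only at 2 years, censoring at crossover with last observation carried forward imputes zero change and biases the arm comparison in a direction that the plan cannot fix

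*Protocol article*

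**What the plan says.** The Data Collection and Outcome Measures section of the protocol article includes "weight, BMI, waist circumference, blood pressure, fasting lipids, fasting glucose, HbA1c, and liver enzymes" among the baseline measurements. It then gives one later time point: "Repeat assessment of blood pressure, body weight, and cardiovascular risk factors (cholesterol profile, glycemic parameters) will be performed at 2 years". A separate list opens with "Additional outcomes to be collected every 6 months will include". That list covers income and employment, quality of life and utilities, satisfaction, the waiting-list questionnaire, the Edmonton obesity stage and economic data. Weight, blood pressure, lipids and glycaemia are not on it. The Follow-up section adds: "Follow-up visits will be scheduled every 6 months for two years and will be performed in-person or by telephone if necessary". Only the 2-year visit is fixed as in person.

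The section comparing surgery with medical and wait-listed patients states: "Two-year mean changes in continuous variables will be compared between the surgical arm and medical or wait-listed controls using unpaired t-tests". Its outcomes are described as similar to those of the wait-list section, which names anthropometric indices, blood pressure, lipids and glycaemic control. Patients who change arm "will be censored at the point of cross over and a last-observation-carried-forward approach to missing data will be used for the primary analysis".

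The wait-list section gives the only reason for carrying values forward: "Because these are self-reported data collected on a semi-annual basis, we will use a 'last-value carried forward' approach". Overall Study Design explains the larger medical arm by saying that "we anticipate an increased rate of censoring in this study arm, as some of these patients will ultimately undergo bariatric surgery".

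**The concern.** Last observation carried forward needs an observation between baseline and the end point. For the questionnaires there is usually one. For the measured clinical outcomes the article shows none. A patient who crosses over is censored before the only repeat measurement, and a patient who misses the 2-year visit never has it. In both cases the last observation is the baseline value, so the 2-year change entered in the t-test is zero. The stated reason for the method, self-reported data collected twice a year, does not describe scale weights, cuff pressures or laboratory values.

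Each arm's mean change is then pulled toward zero by its share of such patients, and the imputed zeros are analysed as if measured. The plan expects those shares to differ between arms. The comparison at stake is Objective 2, the clinical effectiveness of surgery against both control groups. The wait-list analysis (Objective 1) is exposed too if the same approach is applied to its measured outcomes: zeros there bias toward no deterioration, which is the opposite of the study's hypothesis.

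**Working it through.** **Inputs.** From the sample size paragraph of the surgical comparison: surgical 2-year loss 33%, SD 17%, difference 25 points, two-sided alpha 0.05, a printed beta of 0.9 (which must mean power 0.90) and 30% attrition. The implied medical loss is 33 − 25 = 8%. From Overall Study Design: 150 surgical and 200 medical patients.

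**The plan's own figure.** n per arm = 2 × (1.960 + 1.282)² × 17² / 25² = 9.7, rounded up to 10. Then 10 × 1.3 = 13, the stated number, if it is per arm and attrition is added by multiplying. Dividing by 0.7 gives 15.

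**Effect of the rule.** Let f be the share of an arm with no usable 2-year value, m the arm's true mean change and s its SD. With zeros imputed:

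- mean = (1 − f) × m
- variance = (1 − f) × (s² + m²) − [(1 − f) × m]²

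This assumes that the patients given zeros would otherwise have had their arm's average change. It also applies the SD of 17 to the medical arm, for which the plan gives none.

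At f = 0.30:

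- Surgical mean: 0.7 × 33 = 23.1. SD: √[0.7 × (289 + 1089) − 23.1²] = √431.0 = 20.8.
- Medical mean: 0.7 × 8 = 5.6. SD: √[0.7 × (289 + 64) − 5.6²] = √215.7 = 14.7.

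| Share given zero change | Surgical mean | Medical mean | Difference |
|---|---|---|---|
| None | 33.0 | 8.0 | 25.0 |
| 30% in both arms | 23.1 | 5.6 | 17.5 |
| 30% in surgical arm only | 23.1 | 8.0 | 15.1 |
| 30% in medical arm only | 33.0 | 5.6 | 27.4 |

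A simulation with 1,000,000 draws per arm agreed with the means and SDs for 30% in both arms.

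**Direction.** The expected difference is 25 − 33 × f(surgical) + 8 × f(medical). Zeros in the surgical arm shrink it and zeros in the medical arm widen it. They cancel when f(medical) = 33/8 = 4.1 times f(surgical). For assumed shares of 0 to 40% (surgical) and 0 to 50% (medical), the difference runs from 33 × 0.6 − 8 = 11.8 to 33 − 8 × 0.5 = 29.0 points.

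**Power.** With 30% zeros in both arms, the standard error is √(431.0/150 + 215.7/200) = 1.99, so the expected z is 17.5 / 1.99 = 8.8. The number needed for 90% power rises from 10 to 23 per arm before attrition, far below 150 and 200.

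**The case against.** The strongest objection is that the article never says these measures are taken only at baseline and 2 years. The data collection heading points to Additional File 1, which is not shown. Interim visits may be in person, and clinic patients are seen about every 4 to 8 weeks during their 24 to 36 weeks of counselling, so a charted weight might serve as the last observation. This stands as a limit, and the point is conditional on it. But nothing in the article makes clinic-chart values study observations, and wait-listed patients have no such clinic contacts.

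A second objection is that 30% is a sample-size allowance, not a forecast of missed 2-year visits by arm. That also stands: 30% is an assumption here, and the table shows how much depends on where it falls.

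Third, an analysis plan not shown may add sensitivity analyses. It may, but the article already fixes the primary analysis.

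A reader might infer more than the documents support:

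- **That medical-arm crossover hides the benefit of surgery.** The formula gives the opposite: medical zeros alone widen the gap. Any fall comes from surgical patients without a 2-year value, and the plan gives no rate for them.
- **That the true difference is 29 points and shrinks to 20.3.** This takes 4% medical loss, the middle of the 3–5% that the Background gives for lifestyle or drug treatment. The sample size paragraph implies 8%.
- **That the censored medical patients are the committed ones.** Access to surgery does require attendance and adherence, so informative censoring is plausible. But all arms already exclude patients expected to have difficulty with attendance, so this remains an inference.

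**Conclusion.** The concern holds in conditional form. As the article is written, the primary rule assigns zero 2-year change in weight, blood pressure, lipids and glycaemia to crossovers and to patients without a 2-year visit. The rationale given for the method does not cover these outcomes. With the plan's own effect sizes and an assumed 30% of zeros, the 25-point weight difference becomes 17.5, 15.1 or 27.4 points depending on the arm affected. In the first two cases the surgical SD is about 20.8 instead of 17. No direction can be stated without arm-specific rates.

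The conclusion rests on there being no interim measurements in Additional File 1, and on reading the rule as carrying values forward after censoring. The sizes also rest on the average-change and common-SD assumptions above. The 6-monthly outcomes are not affected in this way, except for patients lost before month 6. The test of the weight difference is not at risk; the size of the estimate is.

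**What to change.** In both the wait-list section and the surgical-comparison section, limit last observation carried forward to a sensitivity analysis for outcomes measured only at baseline and 2 years. For these outcomes:

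1. Make the primary analysis multiple imputation, or a likelihood-based model, of the 2-year value. Condition on arm, baseline value, baseline covariates and the 6-monthly data, and set post-crossover values to missing.
2. Where a pre-crossover clinic weight or laboratory value is already charted, use it only as an imputation predictor. Entering it as the outcome would be carrying forward again.
3. Report an as-enrolled analysis with actual 2-year values as a sensitivity analysis.
4. If Additional File 1 does schedule interim measurements, say so and name them.

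No new visits are needed. The price is somewhat more analysis work, abstraction of charted values where they are used, somewhat wider confidence intervals, and reliance on data being missing at random given what was collected. For wait-listed patients, who may have no clinic chart values, the imputation rests on baseline and questionnaire data alone.
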